# Intraperitoneal transplant of Hepatocytes co-Encapsulated with mesenchymal stromal cells in modified alginate microbeads for the treatment of acute Liver failure in Pediatric patients (HELP)—An open-label, single-arm Simon’s two stage phase 1 study protocol

**DOI:** 10.1371/journal.pone.0288185

**Published:** 2023-07-25

## Abstract

**Background:**

Pediatric acute liver failure (PALF) carries a high mortality without liver transplantation (LT) in children. Liver transplantation, though lifesaving, is limited by timely donor organ availability, the risks of major surgery and complications of life-long immunosuppression. Hepatocyte transplantation (HT) improves synthetic and detoxification functions in small animal models. The encapsulation of hepatocytes in alginate protects it from the recipient immune system while the intraperitoneal route of administration allows large volumes to be infused. The safety and possibly short-term efficacy of encapsulated hepatocytes has been observed in a named patient use. A novel type of microbeads (HMB002) has been developed, using a modified alginate and mesenchymal stromal cells (MSCs). Its safety and medium-term efficacy need to be studied in the context of clinical study while optimizing the hepatocyte function and viability using modifications of the alginate and MSCs co-encapsulation.

**Methods:**

A single centre, non-randomised, open-label, single-arm Simon’s two stage study will be conducted to evaluate the safety, biological activity and tolerability of transplantation of a single intraperitoneal dose of microbeads made from an optimum combination of a modified alginate, MSCs and hepatocytes in 17 patients less than 16 years of age with acute liver failure (Stage 1: 9 patients and Stage 2: 8 patient). Safety will be assessed by documenting moderate to severe (including life threatening and death) adverse events due to HMB002 in the first 52 weeks post-procedure. Tolerability will be assessed by observing the proportion of initiated infusions where >80% of infusion is received by the patient. Biological activity will be reflected in patient survival with native liver at 24 weeks post treatment.

**Discussion:**

HMB002, if safe and efficacious in acute liver failure, could be a bridge until the liver regenerates or a suitable organ becomes available. There are multiple advantages to using HT. HT, when delivered by the intraperitoneal route, is less invasive than LT. Hepatocytes from a single donor liver can be used to treat multiple patients. Cryopreserved cells provide an off-the-shelf emergency treatment in PALF. When encapsulated, alginate encapsulation of hepatocytes precludes the need for immunosuppression unlike in LT.

## Introduction

Pediatric acute Liver Failure (PALF) carries a high mortality without liver transplantation (LT) in children [1]. Liver transplantation, though lifesaving, is limited by timely donor organ availability, the risks of major surgery and complications of life-long immunosuppression. Given the regenerative potential of the liver, complete regeneration of the failing liver can be achieved after PALF. This has been demonstrated in auxiliary liver transplantation for PALF where 70% of recipients were able to regenerate their native liver [2]. Hepatocyte transplantation (HT) improves synthetic and detoxification functions in small animal models of acute liver failure [3]. HT, if shown to be safe and efficacious in acute liver failure, could bridge the patient to full recovery if the native liver regenerates or, failing this, support them until a suitable organ is available for LT. HT has multiple advantages over LT. Hepatocyte isolation can yield billions of cells from a single donor liver, that can be used to treat multiple patients. These cells can be cryopreserved for a number of years, providing an off-the-shelf treatment in emergency situations such as PALF. The encapsulation of hepatocytes in alginate protects them from the recipient immune system and precludes the need for immunosuppression, unlike in LT. The intraperitoneal route of administration of microbeads allows large volumes to be infused. HT when delivered intraperitoneally is less invasive than LT. The safety and possibly short-term efficacy of encapsulated hepatocytes has been observed in a named patient use [4]. Mesenchymal stromal cells are known to improve the viability and function of hepatocytes [5, 6]. We have now developed a novel microbead prototype (HMB002) using modified alginate and mesenchymal stromal cells (MSCs) under good manufacturing practice (GMP) standards. Safety and medium-term efficacy (up to 24 weeks while awaiting liver regeneration) need to be studied.

## Materials and methods

### Trial objectives

The trial objective is to evaluate if HMB002 is a safe and effective form of liver support in Pediatric acute liver failure to bridge the patient to native liver survival or liver transplantation. This study will involve intraperitoneal infusion of HMB002. The exact formulation of HMB002 is proprietary but the infusate will consist of alginate beads suspended in transplant medium (1:1 v/v). This is given as a single infusion under ultrasound guidance while observing for any adverse events related to increase in intrabdominal pressure. This will be in addition to standard of care in Pediatric acute liver failure. The beads will be removed using laparoscopy prior to discharge of the patient from hospital, or at time of transplantation, to minimize or eliminate the risk of adhesions within the peritoneal cavity.

#### Primary objective

To evaluate the safety, biological activity and tolerability of transplantation of a single dose of microbeads made from optimum combination of modified alginate, MSCs and hepatocytes to Pediatric patients with acute liver failure.

#### Secondary objective

To establish proof of concept of the transplantation of microbeads made from the optimum combination of modified alginate, MSCs and hepatocytes. To inform the sample size and confidence intervals to design a larger randomized clinical trial.

### Trial registration

EudraCT Number: 2019-000316-29, ClinicalTrials.gov Identifier: NCT05491135.

### Protocol version

Version 3.2 (15th Dec 2022).

### Trial design

This is an, open-label, single-arm, single centre study. A Simon’s two-stage design for a one-sample exact test will be used. We assume a one-year survival rate of 0.20 or less under the null hypothesis, and 0.5 or more under the alternative, with 80% power and 5% type I error rate.

The primary outcome survival measure is set at 24-weeks. Although response to treatment is anticipated to be within the first 4–6 weeks, short to medium term morbidity in children who have been critically unwell in the Pediatric Intensive Care Unit (PICU), Neonatal Intensive Care Unit (NICU) or High Dependency Unit (HDU), is best determined at a longer time point such as 24 weeks. This way almost all possible later deaths due to the acute liver failure (or early post-transplant deaths) will be effectively captured.

#### Sample size

Simon’s two-stage design for a one-sample exact test was estimated, assuming a one-year survival rate of 0.20 or less under the null hypothesis, and 0.5 or more under the alternative, with 80% power and 5% type I error rate. A total of 17 patients will be recruited into the study (at the end of stages 1 and 2). 9 patients will be recruited into the study in the first stage. Once 9 patients have completed their 24 weeks visit, the study will stop for futility if only 2 or fewer patients have survived with the native liver. At the end of the second stage, if 7 or more patients out of the 17 enrolled have survived with native liver at 24 weeks post HMB002 treatment, this will demonstrate proof of concept. DSMB approval is required for progression to Stage 2, where the trial will continue to recruit a further 8 patients. this will be extended to 17 patients as part of the Simon two stage design if there is evidence to support continuation. A long-term follow-up period will be used to monitor safety over a 10-year period post investigational medicinal product (IMP) infusion.

#### Trial duration and flowchart

We will aim to recruit the 17 patients (stage 1 and 2) in approximately 36 months. Each individual patient will be intensively followed up for 52 weeks after receiving HMB002 infusion and then for long-term safety monitoring for a further 9 years. The end of the trial will be defined as the last patient 10-year annual follow up post IMP infusion. The duration of the study will also depend on the progression of the study from stage 1 to stage 2. The schedule of assessment has been explained in Fig 1. The trial flow chart is depicted in Fig 2.

**Fig 1 pone.0288185.g001:**
[figure not shown]
Schedule of assessment. ^a^ Screening and infusion may take place on the same day (Day 0) depending on clinical decision by delegated physician. ^b^ HMB002 infusion will be performed on Day 0 following complete review of all inclusion and exclusion criteria and completion of all pre-infusion checks. See section 4.3 Dosing regimen for details on dosing intervals between subsequent patients. ^c^ Urine or serum pregnancy test (in cases of oliguria) will be performed in females of child bearing potential (FOCBP). FOCBP will only be included after a confirmed negative pregnancy test at screening. Pregnancy is an absolute contraindication to inclusion into the study. However, patients will be hospitalised at the time of screening and until recovery of their native liver or after transplant. Hence, during hospitalisation it is assumed that patients will be sexually abstinent, which is considered a highly effective method of contraception. Therefore, females of child bearing age are eligible for the trial without need for any additional testing or contraception. Should the patient survive with or without liver transplantation, participants will be advised as to highly effective methods of contraception if this is this is appropriate. ^d^ Intra-abdominal pressure will be measured using urinary catheter where possible, at pre-dose (10 minutes prior to start of IMP infusion) and post dose: 1 hr, 8 hrs and 24 hrs (day1). ^e^ IMP Infusion site to be reviewed at 2 hrs, 4hrs, 6 hrs, 8hrs, 12 hrs and 24 hrs post infusion. ^f^ Vital signs include Blood Pressure (BP), Pulse Rate (PR), Respiratory Rate (RR), Temperature and Oxygen Saturation (02 Sats). On Day 0, vital signs will be taken at Pre-dose (approximately 30 mins and 10 mins prior to start of IMP infusion) and Post-dose: 30mins, 1hr, 1.5hrs, 2 hrs, 2.5 hours, 3 hrs, 3.5 hrs 4 hrs, 8 hrs, 12 hrs and 24 hrs (Day1). ^g^ Recording of ventilator settings, ionotropic support (including drugs and dose) and need for renal replacement therapy will be collected as part of standard supportive treatment. On Day 0, supportive treatment data will be collected at pre-dose (30 mins and 10 mins prior to start of IMP infusion and post dose: 30mins, 1hr, 1.5hr, 2hrs, 2.5hrs, 3hrs, 3.5hrs, 4hrs, 8hrs, 12 hrs & 24 hrs(Day 1). ^h^ Clinical Blood Tests 1 include haematology (full blood count and differentials), clotting factors (INR, APTT, fibrinogen) liver function tests (ALT, AST, Creatine Kinase, Total bilirubin, Conjugated bilirubin (only done at screening and if clinically applicable), ALP, Albumin, total protein), urea and electrolytes (sodium, potassium, chloride, urea, creatinine) and Ammonia. At Day 0, bloods will be taken pre-dose (between -4 to -1 hour prior to IMP infusion) and post dose: 1 hr, 8hrs, 16hrs and 24hrs (day1). ^i^ Clinical Blood tests 2 include blood glucose, lactate and blood gases (pH, Partial pressure of O2, Partial pressure of carbon dioxide, standard bicarbonate). On Day 0, these blood will be taken pre dose (10mins prior to start of IMP infusion) and post dose: 1hr, 2hrs, 4hrs, 8hrs, 16hrs, 24hrs (day1). ^j^ Bloods for translational research on Day 0 –to be taken approximately 10 mins prior to IMP infusion and 1 hour post IMP infusion. Aliquots of certain human products (fresh frozen plasma, cryoprecipitate and albumin) administered as part of standard of care will also be sent as controls. ^k^ Neurological Assessment includes Glasgow Coma Scale and Pupil response. ^l^ PedsQL^™^ Quality of Life Inventory questionnaires for parent and child will be optional; completed at screening and week 52 visits. ^m^ The beads will be removed using laparoscopy prior to discharge of the patient from hospital or washed out at the time of transplantation, whichever occurs first. Usually this will be within 4 weeks of the procedure but in any case, microbeads will be retrieved within 24 weeks of HMB002 infusion. ^n^ Live**r** Transplant form will be completed for those patients who go onto receive a transplant within the duration of the study. ^o^ Patients will be discharged from hospital following recovery with either native liver or post liver transplant. Discharge post IMP infusion form to be completed. ^p^ End of study/withdrawal form will be completed following completion of the study or for those patients who did not complete the study. ^q^ All outpatient study visits following discharge, will have a flexible window of +/- 3 days except week 52 visits where +/- 7 days is permitted. ^r^ Long term follow up data will be collected annually within +/- 1 month window. FBC, LFT and abdominal ultrasound will be collected annually until year 5 post IMP. SAEs and associated concomitant medications (except SAEs excluded from reporting) will be collected until end of study.

**Fig 2 pone.0288185.g002:**
[figure not shown]
Trial flowchart. *Interim DSMB meetings as advised by DSMB Chair for the duration of the study. # Study will be terminated if 2 or fewer patients survive with native liver at 24 weeks post HMB002 infusion, after stage 1 of the trial. A total of 17 patients will be recruited into the study (stage 1 = 9 patients and stage 2 = 8 patients).

#### Study setting

Patients will be recruited from a single academic hospital, the Pediatric Liver Centre King’s College Hospital, London. This is one of 3 centres in the UK to which children with acute liver failure are referred. All study visits up to 52 weeks will be conducted at King’s College Hospital (KCH).

#### Eligibility criteria

*Inclusion criteria*.

I. Infant or child (male or female) under the age of 16 years at recruitment.II. Written informed consent obtained from a parent / legal guardian;III. Presence of ALF defined as a multisystemic disorder in which severe impairment of liver function with or without encephalopathy^a^ occurs in association with hepatocellular necrosis reflected as synthetic liver failure in a child with no recognised underlying chronic liver disease. Children must fit one of the ALF categories as described in Appendix 1^b^ in S2 File;IV. Willing and able to comply with the study visit schedule.

a—Diagnosis of encephalopathy may not be possible in infants and small children

Other parameters become more relevant

b—Children who meet inclusion criteria as above but would otherwise not be suitable for liver transplant because of progressive neurological disease for example, will not be excluded from the trial unless they also have exclusions as detailed in criteria for the trial.

*Exclusion criteria*.

I. Severe ascites causing high intra-abdominal pressure and / or respiratory compromise;II. Intra-abdominal sepsis suspected or proven;III. Clinical condition too unstable to tolerate procedure without compromise;IV. Proven pre-existing allergy or intolerance to alginate on medical history;V. Proven pre-existing allergy to gentamicin on medical history;VI. Intraperitoneal or intra-abdominal malignancy;VII. Adhesions or fistulae to anterior abdominal wall;VIII. Children who weigh in excess of 33kgIX. Pregnant or lactating patients (positive pregnancy test for females of child bearing potential at screening).X. Female patients of childbearing potential who are not willing to use highly effective methods of contraception to prevent pregnancy or abstain from heterosexual activity for 52 weeks post treatment.XI. Male patients who are not willing to use an effective method of contraception (condom, vasectomy, sexual abstinence) for 52 weeks post study treatment, when engaging in sexual activity with a female of childbearing potential;XII. Participation in concurrent therapeutic trial for PALF;XIII. Imminent liver transplantation expected within 12 hours of infusion;XIV. Total hepatectomy;XV. Dependent on extracorporeal membrane oxygenation;XVI. Previous liver transplant

#### Replacement of subjects

Eligible patients who do not receive IMP infusion following screening, or who do not tolerate the procedure will be replaced for the purpose of maintaining trial numbers.

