*Dosing regimen*. The route of administration of the product is intra-peritoneal with a 14-16G cannula under ultrasound guidance by a physician. A single dose (weight-dependent) will be used in all patients. There are no increments of dosage. The dose will be administered as soon as possible following parental/legal guardian consent and screening of the patient, as these patients are critically ill. The infusion will be administered at a rate of approximately 150-200ml per hour under antibiotic prophylaxis and close monitoring. This dose has been determined using in vitro, in vivo and previous clinical pilot experience. An infusion of more than 80% of the final product for the patient will be considered as a completed infusion.

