#### Outcomes

*Primary endpoints*.

Safety: Moderate to severe (including life threatening and death) adverse event occurrences due to product in 1^st^ 52 weeks post procedureTolerability: assessed by the proportion of initiated infusions where >80% of the infusion is received by the patient.Biological activity: Survival with native liver at 24 weeks post treatment.

*Secondary endpoints*.

Change in blood marker levels including haematological, biochemical and coagulationbaseline to 52 weeks post treatment.Quality of life measuresPatient survival with native liver at 52 weeks post treatmentPatient survival with transplanted or native liver at 24- and 52-weeks post treatment.

*Exploratory end points*

To assess the assay ‘Hepamorph’ which distinguishes the recipient liver cell derived proteins from the donor liver cell derived proteins using a targeted mass spectrometry approach.To analyse viability and function of microbeads which are retrieved from the intraperitoneal cavity either at laparoscopy or transplant for phenotype ex vivo.

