#### Statistical methods

*Analysis of primary endpoints*.

The number of moderate to severe adverse event occurrences due to product in 1^st^ 52 weeks post procedure will be reported.The proportion of initiated infusions where >80% of the infusion is received by the patient will be reporter.Survival with native liver at 24 weeks post treatment and 95% confidence interval will be reported as one minus the cumulative incidence of death with native liver, liver transplant being considered as competing events.

*Analysis of secondary endpoints*.

Change in blood marker levels (haematological, biochemical and coagulation) will be reported from baseline to 52 weeks post-treatment.Change in quality-of-life measures levels will be reported from baseline to 52 weeks post treatment.Survival with native liver at 52 weeks post treatment and 95% confidence interval will be reported as one minus the cumulative incidence of death with native liver, liver transplant being considered as competing events.Overall survival and 95% confidence interval at 24 weeks and 52 weeks post treatment will be estimated using the Kaplan-Meier method.

*Other reporting*.

A comprehensive report of the collected examination items will be provided according to the protocol’s schedule of assessment.

An analysis of outcomes will be conducted at stage 1 Go/No Go time point for DSMB safety review, when the 9^th^ patient has completed their 24-week post IMP study follow up.

According to the trial design, a first analysis will be conducted once 9 patients have received the proposed treatment and completed 24 weeks of follow up. If two or fewer survive with the native liver at 24 weeks after treatment then the trial will be stopped at this stage. Once 52-week follow up is completed for all 9 patients, primary and secondary endpoint will be analysed according to the protocol specification. If more than 2 survive with the native liver at 24 weeks after treatment, then recruitment will continue to a total of 17 patients (stage 2). Once 52 week follow up will be completed for all 17 patients having received the treatment, primary and secondary endpoints will be analysed according to the protocol specification.

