#### Methods for additional analyses

There are no subgroups to analyse. Calculation of time to death will consider transplantation as a competing risk.

*Methods in analysis to handle protocol non-adherence and missing data*. This is an early phase trial, so that analysis will be conducted per protocol on patients with available data. Patients with incomplete data will therefore be discarded. Patient accrual will be continued until the required number of patients with complete data is reached.

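### The replacement rule lets children whose infusion was started but not tolerated drop out of the 9/17 native-liver survival count, and no other rule keeps them in

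*Protocol article*

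**What the plan says.** Under Replacement of subjects, the article says "Eligible patients who do not receive IMP infusion following screening, or who do not tolerate the procedure will be replaced", the stated purpose being "for the purpose of maintaining trial numbers". Children never infused and children who do not tolerate the procedure are named as two groups and treated alike.

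Tolerability is part of the primary objective. Under Outcomes it is a primary endpoint, "assessed by the proportion of initiated infusions where >80% of the infusion is received by the patient", and Statistical methods reports the same proportion. The dosing text under Intervention adds: "An infusion of more than 80% of the final product for the patient will be considered as a completed infusion".

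The Sample size section sets the survival rule: stop if 2 or fewer of the first 9 survive with native liver at 24 weeks, and declare proof of concept if 7 or more of the 17 enrolled do. Statistical methods instead refers to 17 patients who received the treatment.

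On non-adherence and missing data, Methods for additional analyses says "analysis will be conducted per protocol on patients with available data", then "Patients with incomplete data will therefore be discarded", then "Patient accrual will be continued until the required number of patients with complete data is reached".

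**The concern.** Replacing a child who was never infused does no harm to these endpoints, because that child was not exposed. Replacing a child whose infusion was started is different. The decision comes after exposure, in an open-label trial, on a criterion that the article does not define. The replaced child's place among the 9 or the 17 goes to someone else, so the survival rule is applied to children selected for having tolerated the product. If non-tolerators do worse, the rule is tested at a higher survival rate than the one in all infused children, and its type I error no longer holds. The stage 1 decision rests on nine children, so one replacement can turn 2/9 (stop) into 3/9 (continue).

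The rule also sits awkwardly beside the tolerability endpoint, since the children it replaces appear to be those that the endpoint would count as failures. The per-protocol and discard rules do not settle whether they stay in that proportion or in the 52-week summary of product-related adverse events.

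**Working it through.** **Inputs from the article.** n1 = 9, stop if 2 or fewer; N = 17, so n2 = 8; success if 7 or more; p0 = 0.20, p1 = 0.50; 5% type I error; 80% power.

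**Inputs assumed.** The non-tolerance rate t among started infusions is taken as 5% to 30%. Native-liver survival s in non-tolerators is taken as 0, 0.10 or 0.20. The article gives neither.

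**Step 1: the plan's own design.** The probability of declaring proof of concept at true rate p is

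R(p) = Σ over x = 3 to 9 of P(X1 = x) · P(X2 ≥ 7 − x), with X1 ~ Bin(9, p) and X2 ~ Bin(8, p).

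- R(0.20) = 0.034, within the stated 5%.
- R(0.50) = 0.806, matching the stated 80%.

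The sample size reproduces and is not in question.

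**Step 2: effect of replacement on the survival rule.** Let overall native-liver survival among all infused children be 0.20. If non-tolerators are replaced, the rate among those kept is

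p_kept = (0.20 − t·s) / (1 − t).

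For example, t = 0.20 and s = 0 give 0.20/0.80 = 0.25, and R(0.25) = 0.098. With t = 0.20 and s = 0.10, p_kept = 0.18/0.80 = 0.225 and R = 0.061.

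| Non-tolerance t | s = 0 | s = 0.10 | s = 0.20 |
|---|---|---|---|
| 5% | 0.044 | 0.039 | 0.034 |
| 10% | 0.057 | 0.045 | 0.034 |
| 20% | 0.098 | 0.061 | 0.034 |
| 30% | 0.172 | 0.086 | 0.034 |

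On this grid the nominal 5% is passed from t = 10% when s = 0 and from t = 20% when s = 0.10. It is never passed when non-tolerators survive at the same rate as the others.

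**Step 3: tolerability, only if it were counted on the maintained 17.** The expected number of replacements before 17 completers is 17·t/(1 − t): 0.9, 1.9, 4.3 and 7.3 at t = 5, 10, 20 and 30%. After four replacements, all initiated infusions give 17/21 = 81.0% (exact 95% CI 58.1 to 94.6). The maintained 17 would give 17/17 = 100% (80.5 to 100).

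**Step 4: power if all infused children are counted.** If 0.50 is the overall rate in infused children, power stays at 0.806. If it is the rate in completers only, the overall rate is (1 − t)·0.50 + t·s. With s = 0.10:

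- t = 10%: 0.45 + 0.01 = 0.46, R = 0.706.
- t = 20%: 0.40 + 0.02 = 0.42, R = 0.586.

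**The case against.** A reader might infer that tolerability must come out at 100%, that safety loses the children who reacted, and that all three primary endpoints are therefore biased. The article does not support this.

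- **Tolerability.** The abstract, the Outcomes section and the Statistical methods section all define it on initiated infusions. Read literally, a failed infusion stays in the denominator whether or not the child is replaced. The replacement rule is about numbers and does not say that data are removed.
- **Safety.** Adverse events are collected from consent to week 52, and a discontinued infusion is one of the recorded actions. The halting rule for product reactions is not limited to completers, and the DSMB sees individual and cumulative data. At most, the composition of the final summary is unclear.
- **Per protocol.** The article never defines this as more than 80% received. A child with a partial infusion can have complete 24- and 52-week data.
- **Tolerating the procedure.** The phrase is undefined. The exclusion criteria and pre-infusion checks use similar wording for fitness before infusion, so it could include failure before any product is given. Equating it with 80% or less received is an inference.
- **Evaluable set.** For a phase 1 proof of concept, an efficacy set of treated and evaluable patients is defensible if all exposed children are reported for safety and tolerability.

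These points hold, and they narrow the concern. They do not rescue the survival count. The article names non-tolerators separately from children not infused, which most naturally includes started infusions. It replaces them within the 9 and the 17, and it nowhere says that they stay in. Nor does it declare an evaluable-set analysis, and its success rule refers to 17 enrolled.

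**Conclusion.** The point holds for the native-liver survival rule. As written, exposed children can be taken out of the 9/17 count after the event, which conflicts with the enrolled-patient success rule and sits badly with an endpoint on initiated infusions. For tolerability and the adverse event summary, the finding is an ambiguity to resolve and not a demonstrated bias.

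The size depends on two assumed quantities, as tabulated above: from no inflation when non-tolerators survive like the others, to a type I error of 0.172 at 30% non-tolerance with no native-liver survival among them. The calculation also assumes that not tolerating the procedure refers to started infusions. This should be fixed, and doing so is easy because the article reports that recruitment has not begun. It does not invalidate the design.

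**What to change.** 1. In Replacement of subjects, limit replacement to children in whom no infusion was started.
2. In the paragraph on non-adherence and missing data, state that every child with an initiated infusion stays in the safety and tolerability denominators and takes one of the 9/17 places in the survival rule, whatever fraction was received. Children who received more than 80% can form a supportive analysis.

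This is about one sentence in each place and changes analysis denominators only. The design keeps its exact type I error of 0.034. The price should be stated openly: if the 0.50 alternative was meant for completers only, power among all infused children falls from 0.806 to about 0.71 at 10% non-tolerance and 0.59 at 20%, taking 10% native-liver survival in non-tolerators. The sponsor should therefore also say which population the 0.20 and 0.50 describe.
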